#### Sample size and eligibility criteria

A sample size calculation was conducted using the Horatio Computer Software program [57]. The inclusion of 50 parent-child dyads was deemed sufficient to detect a large effect size (d = 0.8) of a two-level, between groups independent variable, 79% of the time, using a 0.05 alpha level.

To be eligible for this study, parents/guardians must have a BMI of > 25 kg/m^2^, live with their child (aged 2.5–10) for at least 5 days of the week, speak English, and are comfortable using a computer for data collection purposes. Because adolescence spans 10–19 years [58], the research team decided targeting children aged 10 and under for the study described in this paper would be the most impactful. If there are two parents and two children in a family who meet the inclusion criteria, they are permitted to participate as two separate dyads. In the case where two parent-child pairs within the same household are both randomized to receive the intervention, the parents will work with two different coaches.

#### Certified professional co-active coaches (CPCCs)

A total of 16 certified CPCCs have been recruited through the research team’s network to deliver the intervention (three coaching sessions per month, for three months) to parents assigned to the intervention group. The lead researcher informs interested coaches about the study design and outcomes being measured and answers any questions or concerns coaches may have. Coaches involved in the study are assigned between 1 and 3 participants based on how many they feel they can work with over the duration of the study. Upon completion of the intervention, coaches receive an honorarium for each participant with whom they have worked.

It is important that all coaches are certified in Co-Active coaching because: (a) it is an accredited method of coaching, (b) it is consistent with respect to training, in that all coaches are taught the same way and use consistent tools; and (c) this particular coaching method has been shown to be effective in changing health behaviours [35].

### Participants and recruitment

Ethical approval has been obtained from the Office of Research Ethics at the host institution. Participants are being recruited via poster advertisements at various locations including: clinics and medical offices, childcare centers, pharmacies, the local health unit, Young Men’s Christian Association (YMCA) sites, libraries, recreation centers, Ontario Early Years Centers, and community organizations (including local businesses). In addition, a radio advertisement is airing, and recruitment posters are advertised on Facebook groups/pages, Twitter, Kijiji, and in a local parenting magazine. Once participants contact the researcher, the study is explained in more detail, and the researcher asks several questions to determine eligibility. When a parent-child dyad is determined as eligible to participate, a baseline appointment is made in order to conduct the parent’s measurements (height, weight, and waist circumference), inform the parent of group assignment, sign consent forms, provide the dyad with pedometers, and further explain how the study will unfold.

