## Methods

### Study design

This 3-month, single centre, randomized controlled trial (in accordance with SPIRIT guidelines [56]) is currently underway and aims to improve PA and nutrition behaviours within the family unit. Using a single blind, block randomized design via computer randomization (using an online random sequence generator), parent-child dyads are assigned to either: coaching plus health education (intervention) or health education alone (control). The blocked randomization design ensures an equal proportion of dyads are assigned to each group. Only the lead researcher is aware of allocation assignment; parent participants are made aware of their group assignments at their baseline appointments.

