#### Data collection

Rolling enrollment has been adopted, making the data collection periods tailored to each individual in the study. Data are being collected at baseline (i.e., one week prior to the start of the intervention); six weeks into the intervention; immediately post-intervention (i.e., three months); and six months post-intervention. All data is being entered electronically at the host university, on a secure server. Consent and other written forms are stored and locked in a secure drawer, in a locked office, at the host university. In order to maintain confidentiality and anonymity, participants are assigned a unique identification code upon registering in the study. Participant files will be kept in storage for up to 5 years after completion of the study. Baseline and follow-up assessments are conducted at the host university or at the participant’s home by the lead researcher and a research assistant. An email link is sent to parent participants asking them to complete the questionnaires, and email and telephone reminders are conducted one and two weeks later if no response is received. If there is no response, it is assumed that the participant has missed the data collection time and contact re-commences at the next follow-up time. If a participant cannot be contacted after three consecutive communication attempts, it is assumed that they are lost-to-follow-up. A grocery store gift card is provided to participants who complete the study. An overview of study measurements and time points can be found in Table 1.

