### Health education sessions for parents

Participants in the control group receive 6 online health education sessions, with three sessions focused on PA (i.e., benefits of PA; guidelines; sedentary behaviour; sleep; physical literacy; ideas for increasing PA in daily lives of parent and child; and local resources to help increase PA), and three sessions focused on nutrition (i.e., understanding nutrients and nutrition labels; eating with children; positive food environments; challenges to healthy eating; and healthy eating on a budget). The research team, who has collective expertise in each area, created and reviewed these sessions.

The online health education sessions are open to participants upon entry to the study, and parents are asked to engage in their next lesson approximately 7–10 days after their previous one. As this is intended to be a person-focused study, online lessons are being used to best accommodate the realities of each participant’s schedule. The completion of each lesson is being tracked by participant login and duration, and by a “What is the most important lesson I took from this session?” question that they are asked to complete and submit at the end of each module.

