### Data analysis

SPSS (version 24) will be used to conduct a repeated measures MANCOVA to assess differences within groups, and a two-way ANCOVA to assess differences between groups, where baseline data will be the covariate, with differences analyzed using the post-hoc Least Square Differences method. As socioeconomic status (SES) has an impact on nearly all health issues, including obesity, and understanding its impact in the proposed project is necessary, a general linear model utilizing SES as covariate will be completed. Classification for SES will be based on education and low income cut off scores (LICO) utilizing Statistics Canada’s definition. The semi-structured interview responses from parents, to determine changes in family health behaviours and overall program experiences, will be analyzed in NVivo by two independent researchers. Inductive content analysis (a method in which patterns, themes, and categories emerge from the data, without an existing framework; [76]) will be employed to identify feedback themes. This process involves open coding, in which data is read through several times, and as many headings as necessary are written down to describe all aspects of the content [77]. The headings are then collected on a coding sheet, and categories are grouped and sorted into higher order headings [78, 79]. Data are classified into groups in order to help describe a phenomenon, increase understanding, and generate knowledge [80]. Once categories are decided upon, the two researchers compare headings and come to consensus on final themes, with the support of NVivo software.

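### The baseline step count is recorded after parents learn their group and then serves as the ANCOVA covariate; disclosure is also listed ahead of consent

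*Protocol article*

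**What the plan says.** All references are to the protocol article.

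- **Participants and recruitment.** Screening comes first: "the researcher asks several questions to determine eligibility". Once a dyad is judged eligible, "a baseline appointment is made in order to conduct the parent’s measurements (height, weight, and waist circumference" is the opening of the list of tasks for that visit. The list goes on to "inform the parent of group assignment, sign consent forms, provide the dyad with pedometers, and further explain how the study will unfold".
- **Study design.** "Only the lead researcher is aware of allocation assignment; parent participants are made aware of their group assignments at their baseline appointments".
- **Data collection.** "Data are being collected at baseline (i.e., one week prior to the start of the intervention". The people doing the assessments are given as follows: "Baseline and follow-up assessments are conducted at the host university or at the participant’s home by the lead researcher and a research assistant".
- **7-day step count** (a primary outcome measure). Parent and child each wear a pedometer during waking hours for one week at every time point and reset it to zero each morning.
- **Health education sessions for parents.** "The online health education sessions are open to participants upon entry to the study".
- **Data analysis.** Groups are compared by ANCOVA, "where baseline data will be the covariate".

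**The concern.** ANCOVA on a baseline value is safe when the assignment cannot have influenced that value. Here it can. Parents hear whether they will be coached, take the pedometers home, and then produce the baseline week themselves. A parent about to start coaching may walk more that week, or may put off any change until coaching begins. A parent told they will get education only may lose interest or may compensate. Any such difference between arms enters the covariate and is carried into the adjusted treatment effect.

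The listed order raises a second problem. If the group is disclosed before consent is signed, a parent who came for coaching and hears that it is not on offer can leave without signing. Such refusals would fall unevenly between arms. Because the parent never consented, they might appear nowhere in the trial's records. The Strengths and limitations section already expects more dropout from control conditions.

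**Working it through.** **1. Order of events.** Study design and Participants and recruitment both put disclosure at the baseline appointment. Participants and recruitment puts the handing out of pedometers at the same appointment. The step week takes seven days from then. Whatever the order within the visit, the baseline step count follows disclosure. This does not depend on reading the list as chronological.

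**2. The plan's own figure.** Inputs from Sample size and eligibility criteria and the Abstract: 50 dyads, 1:1 (25 per arm), d = 0.8, alpha 0.05. The noncentrality is 0.8 × √(25 × 25 / 50) = 2.83 on 48 df. The two-sided t test gives 79.1% power, which matches the stated 79%. That figure is not in dispute. It supplies the scale used below.

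**3. Bias in the adjusted step-count effect.** Let β be the within-group slope of follow-up on baseline (both in SD units) and δ the difference between arms in baseline steps caused by disclosure. The ANCOVA estimate is about the true effect − β × δ. The documents give neither β nor δ, so both are assumed.

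| β | δ (SD) | bias = β × δ | share of 0.8 | actual type I error at nominal 5% |
|---|---|---|---|---|
| 0.5 | 0.1 | 0.05 | 6% | 5.5% |
| 0.5 | 0.2 | 0.10 | 12.5% | 6.8% |
| 0.5 | 0.3 | 0.15 | 19% | 9.1% |
| 0.7 | 0.1 | 0.07 | 9% | 6.3% |
| 0.7 | 0.3 | 0.21 | 26% | 17.2% |

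The type I error takes a true effect of zero and a standard error of √(1 − β²) × √(2/25 + δ²/48), with 47 df. For β = 0.5 and δ = 0.2 that is 0.866 × 0.284 = 0.246, so the noncentrality is 0.10 / 0.246 = 0.41 and the error rate is 6.8%. Widening the assumptions to β of 0.3 to 0.7 and δ of 0.1 to 0.5 gives a bias of 0.03 to 0.35 SD and a type I error of 5.1% to 37.6%.

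The sign follows δ. If the coaching arm steps up in the baseline week, the estimated effect is too small. If the control arm does, it is too large.

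**4. Refusal after disclosure.** The number is again assumed. Three control refusals would be 3/25 = 12% of an arm. If they are not replaced, 25 against 22 gives a noncentrality of 0.8 / √(1/25 + 1/22) = 2.74 on 45 df and power of 76.4%. Selection matters more than the lost numbers. If the least motivated fraction q of controls declines and motivation correlates r with outcome, the control mean moves by r × φ(z_q) / (1 − q). For q of 0.1 to 0.2 and r of 0.3 to 0.5 this is 0.058 to 0.175 SD. If the most motivated decline instead, the shift has the opposite sign.

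**The case against.** The strongest reply is that the list in Participants and recruitment states the purposes of a visit and is not labelled as a sequence. Read literally, it would also put body measurements before consent. The article says that the trial follows SPIRIT, and Table 1, where the schedule would be set out, is not shown. This stands in part: the order of disclosure and consent needs clarifying. But no section puts consent first, and the list as written has an assignment to disclose when the parent decides whether to sign. The step-count point does not depend on this order.

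Several stronger readings are tempting, and the documents do not support them:

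- **The screener knows the coming assignment.** Screening is done by a member of the research team who is not identified as the lead researcher, and nothing says that the next assignment is visible at screening. A failure of concealment is not shown.
- **Lessons are open during the baseline week.** They open on entry to the study, but entry is not defined, and baseline is placed a week before the intervention starts. Both arms also receive the same six lessons, so early access alone would not differ by arm.
- **Parents are excluded on measured BMI after assignment.** Eligibility is settled by questions before the visit is booked, and no later exclusion is described.
- **All baseline covariates are contaminated.** Height, weight and waist are listed ahead of disclosure. The text does not time the questionnaires or the diet recall against it. Only step counts are shown to follow disclosure.

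It is also fair to say that the size rests on assumed inputs. Only d = 0.8 and 25 per arm come from the article.

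**Conclusion.** The point holds for step counts. The baseline week of parent and child follows disclosure of the arm, and that post-disclosure value is the covariate for a primary outcome. On assumed slopes of 0.5 to 0.7 and shifts of 0.1 to 0.3 SD, the adjusted effect moves by 0.05 to 0.21 SD (6% to 26% of 0.8). The direction is unknown, so the bias cannot be presumed conservative. These figures illustrate what is possible and do not estimate what has happened.

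The enrolment point holds in a qualified form: as listed, an assignment exists when consent is signed, so a parent can refuse because of it and leave no trace. If consent is in practice signed before disclosure, this part falls away and the text needs only correction.

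Three matters are for the sponsor to confirm and are not findings: whether the person who screens and enrols can see the coming assignment, when the lessons unlock relative to the baseline week, and whether BMI, questionnaires and diet recall are completed before disclosure.

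The change is worth making while recruitment continues, because no later analysis can recover unrecorded refusals or a step count taken before disclosure.

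**What to change.** **For remaining dyads**, use this order:

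1. Sign consent.
2. Confirm measured BMI and complete the baseline measures, including the seven-day pedometer week.
3. Release and disclose the assignment by email or telephone.
4. Unlock the lessons.

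Release the assignment at the end of the pedometer week, or at a fixed cut-off, even if questionnaires are outstanding. Data collection allows reminders at one and two weeks and tolerates non-response, so waiting for complete data could block randomisation. Keep the coming assignment concealed from whoever screens and enrols, for example in sequentially numbered sealed envelopes.

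**For dyads already enrolled**, report any refusals after disclosure that can be identified, and record for each dyad whether the step baseline preceded disclosure. Add a sensitivity analysis of follow-up step counts without the post-disclosure baseline covariate. Change from baseline is no substitute, because it would carry the whole shift δ in place of β × δ.

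**Cost.** Disclosure and the start of the intervention are delayed by about one week, possibly slightly more, and an ethics notification is needed. No extra visit is needed. The unadjusted analysis is less precise: at slopes of 0.5 to 0.7 its standard error is larger by a factor of about 1/√(1 − β²), that is 1.15 to 1.40. It therefore belongs beside the ANCOVA as a sensitivity analysis.

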#### Data collection

Rolling enrollment has been adopted, making the data collection periods tailored to each individual in the study. Data are being collected at baseline (i.e., one week prior to the start of the intervention); six weeks into the intervention; immediately post-intervention (i.e., three months); and six months post-intervention. All data is being entered electronically at the host university, on a secure server. Consent and other written forms are stored and locked in a secure drawer, in a locked office, at the host university. In order to maintain confidentiality and anonymity, participants are assigned a unique identification code upon registering in the study. Participant files will be kept in storage for up to 5 years after completion of the study. Baseline and follow-up assessments are conducted at the host university or at the participant’s home by the lead researcher and a research assistant. An email link is sent to parent participants asking them to complete the questionnaires, and email and telephone reminders are conducted one and two weeks later if no response is received. If there is no response, it is assumed that the participant has missed the data collection time and contact re-commences at the next follow-up time. If a participant cannot be contacted after three consecutive communication attempts, it is assumed that they are lost-to-follow-up. A grocery store gift card is provided to participants who complete the study. An overview of study measurements and time points can be found in Table 1.

**Table 1 Tab1:**
[figure not shown]
Study schedule of enrolment, interventions, and assessments

### Health education sessions for parents

Participants in the control group receive 6 online health education sessions, with three sessions focused on PA (i.e., benefits of PA; guidelines; sedentary behaviour; sleep; physical literacy; ideas for increasing PA in daily lives of parent and child; and local resources to help increase PA), and three sessions focused on nutrition (i.e., understanding nutrients and nutrition labels; eating with children; positive food environments; challenges to healthy eating; and healthy eating on a budget). The research team, who has collective expertise in each area, created and reviewed these sessions.

The online health education sessions are open to participants upon entry to the study, and parents are asked to engage in their next lesson approximately 7–10 days after their previous one. As this is intended to be a person-focused study, online lessons are being used to best accommodate the realities of each participant’s schedule. The completion of each lesson is being tracked by participant login and duration, and by a “What is the most important lesson I took from this session?” question that they are asked to complete and submit at the end of each module.

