### Co-active coaching plus health education intervention

Participants in the intervention group receive the same six health education sessions described above, plus Co-Active coaching. Parent participants create a schedule with their coach to receive nine, 20-min, one-on-one, telephone-based coaching sessions (3/month for 3 months) focusing on the agenda of the parent’s choosing. Parent participants are matched with a CPCC and together, they create a schedule to engage in nine, 20-min, one-on-one telephone-based coaching sessions (3/month for 3 months). Thereafter, the participant calls the CPCC at the pre-arranged time and at the start of the conversation the client is responsible for identifying the agenda on which they want to focus during that session. The coach has been asked to use only their CPCC skills, which include but are not limited to asking genuinely curious open-ended questions, reflecting back what the participant says, acknowledging the experience that the participant shares, and championing their progress. For a full review of the Co-active coaching approach, see Co-Active Coaching: Changing Business, Transforming Lives [36].

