### Primary outcome measures

#### 7-day step count

Yamax Digi-Walker SW-650 pedometers are provided to participants (for both parent and child), as this model is used frequently in research [59, 60]. The Digi-Walker SW-650 records steps, calculates distance travelled based on individual stride length, and has a stopwatch. For the purpose of this study, only step-count data are recorded. Participants are asked to wear the pedometer for all waking hours except when swimming or bathing, and to reset it to zero each morning, over the course of one week (7 days; [59]) at all measurement time points.

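### Education lessons open at study entry with no stated hold, so the baseline step week and the emailed baseline questionnaires can be recorded after study treatment has begun

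*Protocol article*

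**What the plan says.** All references are to the protocol article.

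- **Health education sessions for parents** gives the access rule: "The online health education sessions are open to participants upon entry to the study". On pace, it adds that "parents are asked to engage in their next lesson approximately 7–10 days after their previous one". No start day is given for lesson 1. Logins and their duration are tracked.
- **Co-active coaching plus health education intervention** applies the lessons to the other arm as well: "Participants in the intervention group receive the same six health education sessions described above, plus Co-Active coaching".
- **Data collection** defines the baseline time point: "Data are being collected at baseline (i.e., one week prior to the start of the intervention". Questionnaires go out by email link, and "email and telephone reminders are conducted one and two weeks later if no response is received".
- **Participants and recruitment** lists what happens at the baseline appointment besides the body measurements: "inform the parent of group assignment, sign consent forms, provide the dyad with pedometers".
- **7-day step count** has parent and child wear the pedometer "over the course of one week (7 days; [59]) at all measurement time points".
- **Data analysis** compares the groups by ANCOVA, "where baseline data will be the covariate", and assesses within-group differences by a repeated measures MANCOVA.

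**The concern.** The lessons are the whole of the control arm's treatment and part of the coached arm's. A baseline should precede treatment, and the Data collection section says that it does. The access rule points the other way. On the ordinary reading, a parent who has consented, learned the allocation and received pedometers has entered the study. For that parent the lessons are already open while the baseline step week runs.

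Baseline has two uses in the analysis: it is the covariate for the between-group comparison and the starting point for within-group change. If a lesson has already altered behaviour, part of the change is absorbed into baseline and measured improvement is too small. If early lesson use also differed by arm, the covariate would be a post-randomisation variable affected by treatment, and adjusting for it would shift the coaching contrast. Step count is listed among the primary outcome measures. So is the IPAQ, which asks about the past week, so a late baseline answer would describe days on which lessons were available.

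**Working it through.** **The plan's own figure.** The only related number is the power statement. With 25 dyads per arm, d = 0.8 and two-sided alpha 0.05, the noncentral t calculation gives 79.1%, against 79% stated. It reproduces, and this point does not affect it.

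**Order of events that the text fixes**

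1. The baseline appointment covers height, weight, waist, consent, disclosure of group and handing out of pedometers. Call it day 0.
2. The step count needs 7 days with a pedometer, so it runs over days 1–7.
3. Reminders for unanswered questionnaires go out 7 and 14 days after the link. If the baseline link is sent on day 0 (an assumption), answers can arrive around day 14.
4. Lessons are open from study entry. No readable sentence makes access wait for step 2 or step 3.

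Height, weight and waist are taken at the appointment itself and are not affected. The timing of the online diet recall is not stated, so it may or may not be.

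**How many lessons could precede a baseline value**

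Let lesson 1 be taken on day *s* and the gap be *g* days. The number of lessons due by day *D* is floor((D − s)/g) + 1. The article gives g = 7 to 10; *s* is an assumption.

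| Lesson 1 taken | By day 7 (end of step week) | By day 14 (second reminder) |
|---|---|---|
| s = 0, g = 7 | floor(7/7) + 1 = 2 | floor(14/7) + 1 = 3 |
| s = 0, g = 10 | floor(7/10) + 1 = 1 | floor(14/10) + 1 = 2 |
| s = 7, g = 7 | none before the step week ends | floor(7/7) + 1 = 2 |
| s = 7, g = 10 | none before the step week ends | floor(7/10) + 1 = 1 |

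In the first row the second lesson falls only on the last day of the step week. Even if lesson 1 waits a week, a questionnaire answered at the second reminder could follow one or two lessons.

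**What this could do to the estimates (illustration only; none of these inputs is in the article)**

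Suppose lesson 1 raises steps by 500 per day in parents who take it early.

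- Equal early use, say 30% to 60% in both arms: within-arm change is understated by 500 × 0.30 = 150 to 500 × 0.60 = 300 steps/day. The baseline difference between arms is 0, and so is the shift in the coaching contrast.
- Unequal early use, 60% of controls and 30% of coached parents: within-arm change is understated by 300 and 150 steps/day. The baseline gap is 500 × (0.60 − 0.30) = 150 steps/day. With an assumed ANCOVA slope of 0.5 to 0.8, and equal lesson exposure by follow-up, the adjusted contrast moves by 150 × 0.5 = 75 to 150 × 0.8 = 120 steps/day in favour of coaching.
- Against an assumed step SD of 2,000 to 4,000, that shift is 75/4,000 = 0.02 to 120/2,000 = 0.06 SD. The trial is sized for 0.8 SD.

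**The case against.** A reader might infer that the two sections flatly contradict each other. The readable text does not go that far. Entry to the study is not defined, and both statements hold if entry means the start of the intervention period, or if lessons are accessible early but begun later. The one-week lead in the baseline definition matches the 7-day step count, which suggests that the week was meant for measurement. The schedule in Table 1 is not shown and may settle the order. An open lesson is also not a lesson taken, and no instruction tells parents to start on day 0. All of this stands, so the point is that the wording permits overlap, not that overlap is certain.

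A reader might also infer that the coaching effect is biased. That is not supported either. Both arms receive the same six lessons, so equal early use leaves the contrast alone. Bias needs different early use by arm. Parents learn their group at the baseline appointment, so a difference is possible, but nothing in the article shows one. The illustrative shift is small beside the planned effect.

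The questionnaire timing is partly inferred: the reminders are described for all time points, and the date of the baseline link is not given. The step count does not depend on that inference.

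Finally, a rule that locks lesson 1 until every baseline form is in could shut out parents who never respond, and dropping affected dyads from a sensitivity analysis would select on behaviour after randomisation. Both objections are sound, and the fix below allows for them.

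**Conclusion.** The point holds as one of wording and sequence. Study treatment is available to both arms from entry, the baseline step week can only follow the appointment, and no readable sentence holds the lessons back. Some baseline values can therefore be recorded after education has begun, contrary to the stated pre-intervention baseline. The case is strongest for the 7-day step count, next for the emailed questionnaires, and weakest for the diet recall.

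The likely consequence is diluted within-group change and a less clean covariate. Its size cannot be derived from the article; the step figures above are illustrations. Bias in the coaching contrast is conditional on unequal early lesson use. The conclusion assumes that entry is no later than the baseline appointment and that Table 1 does not impose a different order. The change is worth making because it costs little and recruitment is still under way, but the point does not by itself threaten the main comparison.

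**What to change.** **Access rule.** In the health education section, replace the clause that opens the lessons at entry with wording such as: lesson 1 is unlocked in both arms at the start of the intervention period. That start comes once the 7-day baseline step week is over and the baseline questionnaires and recalls have been submitted or the baseline reminder window has closed, whichever of these two comes first. State the day on which that window closes, because the article gives reminder times but no closing date. The cap keeps non-responders from being locked out. Align the baseline definition in the Data collection section with the same start date, and check Table 1 against both.

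**Dyads already enrolled.** Use the tracked login dates to report, by arm, how many baseline step counts, recalls and questionnaires followed the first lesson. Run a sensitivity analysis that keeps all dyads, for example by treating the affected baseline values as missing and imputing them from data that precede the lessons, such as the measurements taken at the appointment. Do not exclude dyads for having opened a lesson early.

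**Cost.** A release setting on the online platform, a sentence or two in the protocol, and one additional analysis from data already collected. The downside is a wait for lesson 1 of about one to two weeks, or up to the close of the reminder window.
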